## Methods

### Aims

The main goal of this project is to implement an innovative community-based PR programme and assess its cost-benefit. The primary objectives are to:1.1.Investigate the short- and medium-term effects of community-based PR programmes, implemented with minimal resources and with local healthcare professionals, in patients and caregiver’s health-related quality of life;1.2.Investigate the cost-benefit of the community-based PR programmes on acute exacerbations and healthcare utilisation, to determine whether the intrinsic perceived social value of such programmes have identifiable benefits and, consequently, measurable economic value for society.

The following secondary objectives will be addressed:2.1To explore the short- and medium-term effects of community-based PR programmes on patients and caregivers’ symptoms, impact of the disease, family adaptability/cohesion, peripheral and respiratory muscle strength, exercise capacity, balance and physical activity.2.2To explore differences between patients and caregivers’ who participate and those who did not participate in community-based PR programmes in relation to dyspnoea, fatigue, cough, impact of the disease, emotional state, health-related quality of life, number of exacerbations, healthcare utilization, family adaptability/cohesion, peripheral and respiratory muscle strength and thickness, exercise capacity, balance and physical activity.2.3To explore associations between patients and caregivers’ outcomes of dyspnoea, fatigue, cough, impact of the disease, emotional state, number of exacerbations, healthcare utilisation, family adaptability/cohesion, peripheral and respiratory muscle strength and thickness, exercise capacity, balance and physical activity, pre-post community-based PR programmes.2.4To investigate the short-term effects of community-based PR programmes on patients’ peripheral muscle (quadriceps and biceps) and diaphragm thickness, cross sectional area, echointensity and motion measured resorting to ultrasound imaging.

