### Data collection

Sociodemographic (age, sex, educational level, marital and working status), anthropometric (height and weight to calculate the body mass index) and general clinical data (long-term oxygen, non-invasive ventilation, medical history, comorbidities to calculate the Charlson Comorbidity Index [45] and medication) will first be collected with a structured questionnaire to characterise the sample and will be followed by a lung function test with spirometry [46].

The primary outcome measure will be health-related quality of life, assessed with the St. George Respiratory Questionnaire (SGRQ) [47] in patients and with the World Health Organization Quality of Life Bref Questionnaire [48, 49] in caregivers. The number of acute exacerbations, healthcare utilisation costs and collateral costs (e.g. transport costs, work absence costs, sickness benefits) will also be collected to conduct the cost-benefit analysis [50].

In addition, the following secondary outcomes will be assessed: symptoms of dyspnoea (modified Medical Research Council Questionnaire [mMRC]) [51], fatigue (Checklist of individual strength [CIS-20]) [52] and Functional assessment of chronic illness therapy – fatigue [FACIT-F]) [53, 54], cough and sputum (Leicester cough questionnaire [LCQ] [55] and Cough and sputum assessment questionnaire [CASA-Q]) [56], impact of the disease (COPD Assessment Test [CAT]) [57, 58], emotional status (The Hospital Anxiety and Depression Scale [HADS]) [59, 60], Family Adaptation and Cohesion Scales [FACES-IV]) [61, 62], peripheral (biceps and quadriceps with the hand held dynamometer, 1 [1-RM] or 10 [10-RM] repetition-maximum) [63, 64] and inspiratory and expiratory muscle strength (respiratory pressure meter) [65], exercise capacity (six-minute walk test [6MWT] and one-minute sit to stand test [1-min STS]) [66, 67], balance (brief-balance evaluation systems test [Brief-BESTest]) [68] and physical activity (accelerometer) [14]. Peripheral muscle (rectus femoris and biceps brachialli) and diaphragm thickness, cross sectional area [69, 70] and echointensity [71], excursion and M-Mode Index of Obstruction (MIO) [72–74], will be measured with ultrasound images – ImageJ and Matlab software. Global rating of change scale [75] for fatigue, cough, sputum, peripheral and respiratory muscle strength and balance will also be collected.

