A cost-benefit analysis will be conducted to determine the economic value of the perceived social value of community-based PR programmes. This analysis allows for the aggregation of both health and non-health benefits and costs of the PR programme and provides useful and quantifiable information [99, 100], not only for patients and health care institutions, but also for decision makers [101].

Focusing on the frequency and length of exacerbations, healthcare utilisation costs and quality of life gains, along with several indirect costs and benefits associated with PR implementation, including productivity loss of patients and caregivers who provide assistance, working, transportation costs, administrative costs, opportunity costs, sickness benefits payed to the patient or professional training and recruiting costs, three complementary data analysis will be held: cost:-effectiveness, −utility and -benefit.

As recent studies on COPD have demonstrated, it is suitable for cost-effectiveness analysis to rest on the ratio *incremental cost per exacerbation/healthcare utilisation avoidance* [102] aiming to compare relative costs and outcomes of PR. Then, to assess the expected impact on patients’ health-related quality of life, cost-utility analysis computes the measures of quality adjusted life years (QALY) [103] and healthy years equivalents (HYEs) [104] and determines the incremental cost per QALY/HYE gained. Finally, to account for the monetary translation of positive and negative effects of community-based PR programmes, cost-benefit analysis will be performed by determining the measures of net present monetary benefit and economic internal rate of return [105], along with a sensitivity analysis to control for the uncertainty on the assessment of costs and benefits associated to the community-based PR programmes [106, 107].

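### Sickness benefits are listed as a cost item beside the lost work they compensate, in a cost-benefit analysis meant to show value to society

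*Protocol article*

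**What the plan says.** The protocol article makes cost-benefit part of the main goal and of a primary objective. Under Aims, objective 1.2 is to find out whether the programmes "have identifiable benefits and, consequently, measurable economic value for society".

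The Data collection section states which costs are gathered: "healthcare utilisation costs and collateral costs (e.g. transport costs, work absence costs, sickness benefits) will also be collected to conduct the cost-benefit analysis". Sickness benefits are classed there as a collateral cost, next to the cost of work absence.

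The section Data management and statistical analysis gives a longer list of indirect costs and benefits, "including productivity loss of patients and caregivers who provide assistance, working, transportation costs, administrative costs, opportunity costs, sickness benefits payed to the patient", followed by training and recruiting costs. The list feeds cost-effectiveness, cost-utility and cost-benefit analyses. The cost-benefit analysis is to report a discounted net money benefit and an internal rate of return, with a sensitivity analysis for uncertainty in costs and benefits.

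Neither section says that sickness benefits are to be netted or left out when lost work is also counted.

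**The concern.** A societal analysis counts resources used up or saved. When a patient is off work, society loses the output of that day. A sickness benefit paid for the day changes who bears the loss: the payer is worse off and the patient better off by the same sum. It adds nothing to the loss.

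The article puts both the loss and the transfer on the cost list of one analysis, twice, and states a societal aim. An analyst who follows the list and enters each item as a cost counts part of the same absence day twice. The separate entry for opportunity costs could repeat the same lost time again, because the article does not say what it covers.

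The net benefit and rate of return are meant to inform decision makers and to support wider provision of pulmonary rehabilitation. An item counted twice in those figures is a fault of accounting. Varying unit values in a sensitivity analysis would not remove it.

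**Working it through.** The article states no unit cost, replacement rate or net benefit, so there is no figure of its own to reproduce. The check is an accounting identity.

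**Inputs**

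- Perspective: society (Aims, objective 1.2).
- Items: work absence costs and sickness benefits (Data collection); productivity loss, opportunity costs and sickness benefits (Data management and statistical analysis).
- Not given: the replacement rate, any money value, and the size or sign of the change in absence. I assume a replacement rate f between 0.3 and 1.0.

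**Step 1: one absence day.** Let W be the value of the work lost and fW the benefit paid.

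- Output lost: −W
- Payer: −fW
- Patient: +fW
- Sum for society: −W − fW + fW = −W

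The correct cost is W, whether the benefit is left out or entered on both sides. If lost work and benefit are both entered as costs, the total is W + fW = (1+f)W. The excess is f as a fraction of the correct value.

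**Step 2: a change in absence.** Let P be the societal value of benefit-paid absence avoided (negative if absence rises). The correct component is P, the double-counted one is P(1+f), and the error is fP. With P set to +100 or −100 units for illustration:

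| f (assumed) | Correct, absence falls | Both counted | Correct, absence rises | Both counted | Error, % of correct value |
|---|---|---|---|---|---|
| 0.3 | 100 | 130 | −100 | −130 | 30% |
| 0.5 | 100 | 150 | −100 | −150 | 50% |
| 0.7 | 100 | 170 | −100 | −170 | 70% |
| 1.0 | 100 | 200 | −100 | −200 | 100% |

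**Step 3: who is affected.** Where no benefit is paid, f = 0 and there is no error. That covers people who do not work. The analysis section speaks of benefits paid to the patient, so caregivers' lost work may not be affected either. If only a share w of the absence value carries a benefit, the absence component as a whole is off by w × f. The article does not give w.

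**Step 4: total net benefit.** The error fP passes unchanged into the net benefit. With arbitrary other benefits of 300 units and programme costs of 250:

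- P = +100: correct net benefit 300 + 100 − 250 = 150. With both counted it is 180 at f = 0.3 and 250 at f = 1.0.
- P = −100: correct net benefit 300 − 100 − 250 = −50. With both counted it is −80 at f = 0.3 and −150 at f = 1.0.

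These totals only show the mechanism. The documents do not supply the figures needed for a real one.

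**The case against.** **The list is a pool of inputs, not a sum.** It feeds three analyses, and a condensed article may leave valuation and netting rules to a fuller plan that is not shown. It also speaks of costs and benefits, so an analyst might enter the transfer on both sides, where it cancels. This stands as far as it goes: the double count is what follows from entering the listed items as costs, and is not a computed result. However, Data collection names sickness benefits as a cost for the cost-benefit analysis in particular, so the list as published needs correcting whatever a fuller plan adds.

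**Other audiences are named.** The article says the results also serve patients, healthcare institutions and decision makers, and sickness benefits matter to a payer. That justifies collecting them. It does not justify adding them to lost work in a figure offered as value to society.

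**The direction is open.** The programme itself takes time: 24 exercise sessions of 60 to 75 minutes (24 to 30 hours) plus six sessions of about 90 minutes (9 hours), or 33 to 39 hours per patient. If benefit-paid absence rose on balance, the same error would understate net benefit. This stands. A reader might infer that the fault always favours the programme, but the documents fix neither the sign of the change nor whether time spent at sessions attracts a benefit.

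**A wider double count is tempting but not supported.** The analysis section opens with "Focusing on the frequency and length of exacerbations, healthcare utilisation costs and quality of life gains, along with several indirect costs and benefits" and says that cost-benefit analysis can add health and non-health consequences. A reader might infer that an avoided exacerbation is credited as an event, as saved healthcare and as better quality of life. The text does not say so. It announces that "three complementary data analysis will be held", gives avoided exacerbations and healthcare use to cost-effectiveness and QALYs or healthy-years equivalents to cost-utility, and nowhere puts a separate money value on an exacerbation. Healthcare savings and quality-of-life gains are different consequences and may both enter a cost-benefit analysis.

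**Nor is the ratio at fault.** A reader might object that healthcare use appears on both sides of "incremental cost per exacerbation/healthcare utilisation avoidance". A net cost per event avoided is an ordinary ratio, and it is not added into net benefit.

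**Conclusion.** The point holds for sickness benefits only. The article lists a transfer payment as a cost beside the lost work it compensates, under a stated societal aim and with no netting rule.

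If both are counted with the same sign, each affected absence day is valued at (1+f) times its societal value. This is 30% to 100% too high for an assumed f of 0.3 to 1.0, and exact where no benefit is paid. Net benefit is too high if benefit-paid absence falls and too low if it rises. The conclusion rests on the societal perspective in objective 1.2 and on both items entering as costs, as Data collection classes them. The effect on total net benefit and on the rate of return cannot be derived from the documents.

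**What to change.** In the section Data management and statistical analysis, state that the societal base case:

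- counts lost work once, as productivity loss of patients and caregivers;
- uses opportunity costs only for time or resources not already in that line;
- excludes sickness benefits as a transfer, and reports them only in a separate payer or social-security view.

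In Data collection, keep sickness benefits among the data gathered, but say that they serve the payer view.

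This is a change of wording and needs no new data. The downside is that the reported net benefit may be somewhat less favourable if the programme reduces absence.

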Data will be collected from patients and caregivers at baseline, at 12 weeks and at 3- and 6-months post-PR. Ultrasound imaging will only be collected at baseline and at 12 weeks in patients from the experimental group. Additional file 2 provides an overview of enrolment, intervention and outcomes to be assessed in each time point.

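### The cost-utility analysis promises patient QALYs and healthy-years equivalents, but the protocol lists no preference-based measure and states no mapping to utilities

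*Protocol article*

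**What the plan says.** The economic part of Data management and statistical analysis announces three analyses: cost-effectiveness, cost-utility and cost-benefit. The cost-utility step is directed at patients' health-related quality of life. It states that "cost-utility analysis computes the measures of quality adjusted life years (QALY) [103] and healthy years equivalents (HYEs) [104", and that it "determines the incremental cost per QALY/HYE gained". This is worded as a commitment, not an option.

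The Data collection section lists what will be measured. Quality of life, the primary outcome, is "assessed with the St. George Respiratory Questionnaire (SGRQ) [47] in patients". Caregivers have a different instrument; theirs is measured "with the World Health Organization Quality of Life Bref Questionnaire [48, 49] in caregivers". For the economic work, "The number of acute exacerbations, healthcare utilisation costs and collateral costs (e.g. transport costs, work absence costs, sickness benefits) will also be collected". The remaining questionnaires cover dyspnoea, fatigue, cough and sputum, family functioning, and "impact of the disease (COPD Assessment Test [CAT]) [57, 58], emotional status (The Hospital Anxiety and Depression Scale [HADS]) [59, 60", with a global rating of change alongside. On timing: "Data will be collected from patients and caregivers at baseline, at 12 weeks and at 3- and 6-months post-PR".

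**The concern.** A QALY is time weighted by a utility on a scale where 0 is dead and 1 is full health. A healthy-years equivalent is built from respondents' own preferences over health profiles, elicited by a gamble or trade-off task. The analysis section promises both. The data section appears to supply neither the weights nor the elicitation.

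An analysis plan written later can choose a model or a covariate. It cannot supply answers to a questionnaire that was never given. If the utility source stays open until the data are in, the conversion from a symptom score to a utility becomes a choice made with results in view, and the cost per QALY depends directly on it.

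**Working it through.** The protocol gives no utility, QALY or cost-effectiveness ratio, so there is no figure to reproduce. The check compares what the analysis needs with what is collected.

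**1. Is there a utility among the listed measures?** The ten questionnaires are:

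- SGRQ: disease-specific quality of life (patients)
- WHOQOL-Bref: generic quality-of-life profile (caregivers)
- mMRC: dyspnoea
- CIS-20 and FACIT-F: fatigue
- LCQ and CASA-Q: cough and sputum
- CAT: disease impact
- HADS: anxiety and depression
- FACES-IV: family functioning

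These are symptom, impact, mood or profile scores, and none yields a preference weight directly. The other measures are physical tests, accelerometry, ultrasound and ratings of change. The items collected for the economics are exacerbations and costs. No standard gamble, time trade-off, value set or mapping appears in the text.

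**2. Which ingredient is missing?** QALY = sum of (utility × time). Time is available: 12 weeks plus 6 months is 12/52 + 0.5 = 0.73 years, with four assessments. Utility is not.

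**3. How much depends on the missing conversion?** This is an illustration only. The utility per SGRQ point and the incremental cost are assumptions, not protocol figures.

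- SGRQ change, from the Sample size section: 37.9 − 31.4 = 6.5 points.
- Assumed path: linear gain to 12 weeks, then held for 6 months. QALY gain = 6.5 × k × [(12/52)/2 + 0.5] = 6.5 × k × 0.615, where k is utility per SGRQ point.
- Assumed incremental cost: 500 currency units.

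| Assumed k | Utility gain | QALY gain | Cost per QALY |
|---|---|---|---|
| 0.003 | 0.0195 | 0.012 | about 41,700 |
| 0.006 | 0.039 | 0.024 | about 20,800 |
| 0.01 | 0.065 | 0.040 | 12,500 |

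The same clinical change and the same cost give ratios that differ by 0.01/0.003 = 3.3 times.

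**4. How much time is there to repair it?** Recruitment began in January 2019 and final data collection is expected in December 2019. Counting back 6 months and 12 weeks from the end of December puts the last baseline visit in early April 2019. If that timetable holds, many or all baseline visits will pass before an amendment takes effect, so for these a mapping is the only remaining source of a utility.

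**The case against.** The strongest reply is that this is a condensed article. A mapping algorithm and value set could sit in a fuller protocol or a health-economic analysis plan. The by-visit schedule is in Additional file 2, which is not shown, and the methods are cited to sources that are not at hand. Part of this stands: the missing mapping alone would be weak ground. It does not cover the missing instrument. The Data collection section works measure by measure, down to ultrasound indices and the software used to read them, and the additional file is described only as an overview of enrolment, intervention and outcomes by time point.

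Four stronger readings are tempting, and the protocol does not support them.

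- *QALYs are impossible.* A reader might infer this, but a prespecified external mapping from SGRQ or CAT could approximate patient QALYs. Only healthy-years equivalents are out of reach by that route.
- *Patients and caregivers lack a common utility scale.* They do have different quality-of-life instruments, but the cost-utility step concerns patients only. No caregiver or pooled dyad QALY is announced.
- *Primary objective 1.2 fails.* That objective concerns cost-benefit on exacerbations and healthcare utilisation. Data for both are listed, and cost per exacerbation avoided needs no utility.
- *The quality-of-life part of the cost-benefit sum fails too.* Quality-of-life gains are among the economic inputs, but the protocol does not say that they are turned into money through QALYs.

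**Conclusion.** The concern holds for the patient cost-utility analysis. As the plan is written, the listed data give no direct utility. Patient QALYs would rest wholly on an external mapping that is not named. If that mapping was developed in one disease, such as COPD, applying it across the mixed chronic respiratory diseases enrolled here is a further assumption. Healthy-years equivalents cannot be obtained.

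The true size is unknown because the protocol fixes no conversion. The 3.3-fold spread in the illustration shows only how strongly the ratio depends on that choice. The conclusion assumes that the instrument list in Data collection is complete.

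The SGRQ primary outcome, the sample size, the clinical group comparisons, cost per exacerbation avoided and the data serving objective 1.2 are untouched. This should be fixed, and soon because visits are passing, but it does not undermine the trial's main results.

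**What to change.** - For patients in both groups, add a short generic preference-based questionnaire (for example EQ-5D-5L) at the remaining scheduled visits.
- For visits already completed, prespecify one published mapping from a collected instrument (SGRQ or CAT), with its value set, before outcome data are examined.
- In the main comparison, use the same utility source in both groups. If measured values were more common in one non-randomised group and mapped values in the other, the difference between sources would be mixed with the difference between groups. Report measured versus mapped values as a sensitivity analysis.
- Delete healthy-years equivalents.
- If neither an instrument nor a mapping is adopted, withdraw the cost-utility analysis and report cost per exacerbation avoided and cost per SGRQ point.

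The cost is a few minutes per visit and a small amendment. The real drawback is that measured and mapped utilities are less comparable with each other than a single source used throughout would be, and baselines already taken cannot be recovered. Dropping the QALY and healthy-years promises needs no new data, but gives up one of the three announced economic analyses.

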## Discussion

This real-world study will focus on enhancing patients’ access to PR by implementing it within their community, with the staff available in local primary healthcare centres and actively involving informal caregivers. It will also compute a measure of cost-benefit of implementing this intervention in the community. This information is needed for advocating the wide dissemination of PR across the world, actively involve and train caregivers and more healthcare professionals in the disease management of patients with CRD.

This study differs from others, by implementing a fundamental intervention for all patients with CRD, at different development stage of their disease, within the community, near their homes and where it is known that this intervention is lacking [38]. Patients with chronic respiratory conditions have been accessing to PR mainly in hospitals where constrains regarding availability, transportation, funding and referral exist [28, 38, 108]. Although community-based PR in patients with COPD has been found to be effective for health-related quality of life [35, 36] and exercise capacity [36], caution interpreting these results is needed as relatively few studies exist and they were conducted in several settings (home, primary healthcare centres, a mixture of more than one setting) with disparities in the structure and components of the intervention, hindering strong conclusions regarding the effects of community-based PR. In other CRD, comparisons across settings are not even possible due to the lack of studies [29, 30, 33]. Recently, a community-based PR programme conducted in a non-healthcare facility with patients with several CRD demonstrated positive effects on patients’ exercise capacity, health-related quality of life, and a reduction in respiratory-related hospital admissions in the 12 months following the programme [108]. However, primary healthcare centres are embedded within the community, have a multidisciplinary team available and most patients and their families have their routine follow-ups in these facilities. Therefore, these community healthcare infrastructures might be ideal candidates to enhance patients’ access to PR but, staff often lacks training and equipment is scarce. This study proposes to deliver a highly structured training to available primary healthcare staff where PR is non-existent, supervise the staff during one programme delivery, using minimal resources, and guide them on the development or acquisition of equipment. This will increase the PR response to patients with chronic respiratory conditions but, will also raise awareness in more healthcare professionals for this intervention. It is also known that caregivers are the main providers of support to these patients [20, 21] and it has been demonstrated that when they are integrated in PR programmes the whole family benefits from it [27]. Therefore, this project will be innovative by empowering healthcare professionals of health facilities where PR programmes are not available, but also by actively involving caregivers in this intervention which together is believed to improve dissemination and sustainability of PR in the community directed to patients with several CRD.

In addition, positive effects are expected to arise from the cost-benefit analysis. The need to increase awareness and knowledge of PR among rulers and decision makers has been widely identified, and an economic evaluation might be able to provide “value-for money” information and promote the dialogue among different stakeholders and consequently wider dissemination of PR programmes [10, 38].

Moreover, the longitudinal design will facilitate analysis of changes over time in a comprehensive set of measures enhancing our knowledge on patients’ evolution. This will also represent the ideal opportunity to explore a wide range of emergent ultrasound measures to assess the short-term effects of PR on the structure and motion of the diaphragm and peripheral muscles (biceps and quadriceps). Ultrasonographic assessment of the rectus femoris muscle (thickness and cross sectional area) has been found to be correlated with muscle strength [70], and some measures of diaphragmatic kinetics have been proposed as promising to study disease progression (e.g., MIO) [73, 74] and prognosis of PR outcomes (e.g. change in the diaphragmatic length of zone of apposition at functional residual capacity ΔLzapp%) [109]. Nevertheless, relatively little is yet known about the potential of the ultrasonographic assessment to assess the effects of PR on peripheral muscle (rectus femoris, biceps brachialis) and diaphragm thickness, cross sectional area [69, 70] and echointensity [71], excursion and MIO [72–74].

It is important to acknowledge the limitations of this study. Although it is intended to implement a real-world study as inclusive as possible and, therefore patients with distinct CRD will be eligible, this might poses challenges during the recruitment and implementation phases. This limitation will be minimised by clarifying and emphasising the inclusion criteria in the meetings with healthcare teams when explaining the study. Additionally, an experienced member in implementing PR programmes will be present in all sessions together with the staff of the primary healthcare centre to help with the personalised interventions. The inclusion of chronic respiratory patients may also underpower the study. To mitigate this risk, power calculations were based only on patients with COPD, since they are the most common population referred to PR programmes. Nevertheless, it will be possible to use data from this study to compute power calculations for other studies.

Another anticipated limitation is the recruitment of caregivers. Caregivers are rarely included in PR programmes therefore, they might not be aware of the possible response that PR can provide not only to patients but for the whole family. The importance of their inclusion will be discussed with patients and caregivers when explaining the study. A written information sheet highlighting the importance of their inclusion will be provided to promote their inclusion.

Moreover, acknowledging the benefits that PR has for patients with CRD, not offering PR to all eligible patients will never be considered. Therefore, the CG will be composed of only those patients who are willing to participate in data collection but do not want take part in the PR programme. This might lead to difficulties in recruiting for the CG. Nevertheless, with the permission of patients and caregivers, a telephone call will be made prior to data collection to minimise dropouts.

A follow-up period of 6 months could be too short to draw conclusions about the medium- or long-term changes in patients’ health and non-health measures, necessary for cost-benefit analysis. However, limited funding is available for the study.

Finally, obtaining cooperation of patients during the ultrasound measurements of the diaphragm might be challenging as these patients often present significant dyspnoea and fatigue levels, limiting their collaboration in the requested breathing manoeuvres.

We expect that this study will enhance the patients’ access to PR and provide an evidence-based insight into the economic benefit of community-based PR in chronic respiratory diseases, through a cost-benefit analysis.

